### 2.4. Study Setting, Recruitment and Consent

This study is being conducted in two urban hospital-based T1D clinics in Kampala, Uganda. Mulago Hospital (“Mulago”) is the national referral hospital and the teaching hospital for Makerere University. Nearby, St. Francis Hospital, Nsambya (“Nsambya”) is a teaching hospital for Mother Kevin Post Graduate Medical School, Uganda Martyrs University. These are the two largest pediatric diabetes clinics in Uganda. Patients are recruited through their pediatric diabetes clinics. At Mulago, T1D care is supported by a pediatric endocrinologist, residents, 2 nurses and a dietitian. At Nsambya, the diabetes team is headed by a pediatrician and is supported by 2–3 nurses plus residents. Each clinic follows about 300 children and young adults age 0–26 years. Nsambya is a private not-for-profit missionary hospital while Mulago is a public government hospital. The patients seen at Nsambya have a moderately higher socioeconomic status than those seen at Mulago, but only a few are able to afford better health care or insurance. Both clinics are supported by the CDiC^®^ program (Changing Diabetes in Children, Novo Nordisk, Denmark), with patients receiving free insulin, 2–3 glucose strips per day for SMBG, measurement of HbA1c levels every three months, diabetes education, and an occasional diabetes camp for psychosocial support. Subjects are recruited by the local diabetes teams from their clinics. Patients are commonly seen in pediatric diabetes clinics up to age 26.

### 2.5. Eligibility Criteria

Eligibility criteria include living in the Kampala, Uganda area, age 4–26 years, T1D (determined by clinical criteria) of at least 12 months duration, receiving insulin therapy, and having access to a cell phone (nearly ubiquitous in Uganda).

Exclusion criteria include those unwilling or unable to be seen monthly at the clinic, pregnant or breast-feeding or likely to become pregnant in the next year, any condition which the investigator feels would interfere with study participation, that the patient already has CGM (very rare in Uganda), and inability to wear the sensor for at least 7 days or return it during the baseline assessment period.

### 2.6. Study Management

Both study groups receive intensive monthly diabetes self-management education, with a focus on pattern recognition and insulin adjustment to prevent hypo- and hyperglycemia. Between visits, they have unlimited availability to contact study personnel by telephone at all times. Participants return used sensors at each visit. All study procedures are performed by trained personnel. CGM is considered a low-risk medical intervention.

Participants wearing the unblinded FreeStyle Libre 2 CGM system are able to see their glucose levels at all times. The research team is able to use these data for insulin adjustment, and participants are taught how to interpret the data. Subjects in the control arm wear the blinded CGM Libre Pro while performing SMBG three times daily for six months. Patients are taught how to interpret SMBG data and the research team uses these data for insulin adjustment. Blinded FreeStyle Libre Pro CGM sensors, placed monthly, are used to provide control data. The study team uploads the de-identified data to a study website and neither participants nor the research teams have access to the blinded sensor data for clinical use until the end of months 0–6, to preserve the blinding.

Participants are prescribed insulin regimens as per the patient’s usual routine. This was generally human NPH and regular insulin. However, analog insulin, longacting Basaglar and Levemir and rapid novorapid are increasingly becoming widely available. No participants in the study will be on premixed insulin. The insulin pens are stored at room temperature for the majority of the participants.

### 2.7. Sample Size Determination

The sample size is determined based on hypothesis testing of the primary efficacy endpoint. The null hypothesis is that the two arms will demonstrate no significant differences in the six-month change in glucose TIR. The alternative hypothesis is that wearing unblinded CGM will have greater improvement in glucose TIR over six months compared to the control arm. We estimate a standard deviation of 16.6% for baseline TIR based on our pilot data [3] and assume a moderate correlation of 0.5 between baseline and 6-month TIR values. A sample size of 144 patients (72 per arm) will have over 90% power to detect a difference of 8.6% in 6-month TIR changes between the two arms at the one-sided significance level of 0.05. To allow a 20% dropout rate, a total of 180 patients will be randomized with planned study completion of at least 144 patients. The sample size will have over 90% power to detect a 5-percentage point difference in the 6-month change from baseline in percent time < 70 mg/dL (3.9 mmol/L) or a 3.5 percentage point difference in percent time < 54 mg/dL (3.0 mmol/L) at the one-sided significance level of 0.05.

### 2.8. Statistical Methods

#### 2.8.1. Primary Efficacy Endpoint

The primary efficacy endpoint is the six-month change in percent TIR. A mixed effects model will be used, with a subject-level random intercept, with the fixed-effect predictors including the time of measurement (0, 6, or 12 month), time-dependent binary indicator for the type of CGM (SMBG with blinded CGM or unblinded CGM), and time-by-CGM-type interaction. Covariates such as age and gender will also included if tested as significant in univariate analysis.

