### 2.3. Overview, Study Design

This randomized, non-blinded, phase 4 clinical trial is programmed as follows. Subjects are assigned 1:1 to the CGM Group or the Control Group. Randomization is stratified by clinic and by age group (4–11, 12–18, and 19–26 years) with approximately equal numbers in each age group and of the two clinic locations. The random numbers were generated by the statistician using a central computer. At baseline, a 1–2 weeks initial assessment is performed where the ability to wear and return the sensor can be demonstrated, as an entry criterion for randomization. After this, 180 children and young adults with T1D will be randomized into the clinical trial in four 12-month cohorts of 45 patients each.

The study design is shown in Figure 1. Half of the subjects (*n* = 90, CGM Group) receive unblinded FreeStyle Libre 2 CGM for the entire 12 months. Half (*n* = 90, Control Group) are given sufficient test strips for three times daily SMBG months 1–6, while wearing blinded CGM for endpoint assessment. For months 7–12 they switch to unblinded CGM. The treatment group is expected to continuously modify their insulin dose and behaviors based on real-time, continuous availability of glucose data. The control group has no access to these data and will base their actions on SMBG measurement alone. For study data analysis, we will use unblinded sensor data from the treatment group and blinded sensor data from the control group that is obtained in the two weeks preceding each monthly visit; thus, the CGM data comparison period will be the same for both groups.

The investigators and the patients are not blinded to treatment arm as there is no practical way to do this. But they are blinded to the comparison data for CGM versus SMBG use until the study is completed. Table 1 lists the schedule of study assessments.

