#### 2.8.4. Additional Analyses

Analysis of demographics and baseline characteristics will be descriptive with appropriate summary statistics calculated. Subgroup analyses for the primary endpoints for sensitivity analyses will be conducted. All primary analyses will follow the intent-to-treat principle. The maximum likelihood estimation method will be used to deal with any missing data, assuming that data are missing at random. Sensitivity analyses will be carried out with various assumptions of missing mechanisms. Unblinded CGM offers the prospect of direct benefit with the potential to reduce hyper- and hypoglycemia in the concerned population and has been shown to be safe and effective in children, and we want to collect data for other variables such as DKA and serious hypoglycemia even if the unblinded CGM has no efficacy on TIR; thus, no interim analysis is planned.

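### The random-intercept primary model assumes one variance and one correlation for TIR across months 0, 6 and 12, so the standard error of the month-6 difference can be misstated in either direction

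*Protocol article*

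**What the plan says.** Section 2.8.1 sets the endpoint ("The primary efficacy endpoint is the six-month change in percent TIR") and the model: "A mixed effects model will be used, with a subject-level random intercept". The fixed effects are "the time of measurement (0, 6, or 12 month"), a "time-dependent binary indicator for the type of CGM (SMBG with blinded CGM or unblinded CGM), and time-by-CGM-type interaction", with age and gender added if significant in univariate analysis. No random slope, residual covariance structure or robust standard error is named.

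Section 2.3 places a treatment change inside the modelled period. Of the controls it says: "For months 7–12 they switch to unblinded CGM". The CGM arm stays on the same device throughout.

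Section 2.7 gives an SD of 16.6 percentage points for baseline TIR and says the authors "assume a moderate correlation of 0.5 between baseline and 6-month TIR values". It gives no SD for month 6 or month 12, and no correlation involving month 12.

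Section 2.8.4 adds: "The maximum likelihood estimation method will be used to deal with any missing data", assuming missing at random. Its sensitivity analyses concern missing-data mechanisms and subgroups, not the covariance.

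**The concern.** A random intercept with independent residuals implies compound symmetry: the same TIR variance at every visit and the same correlation for all three pairs of visits. The design gives reasons to doubt this.

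- Controls change monitoring method between months 6 and 12 while the CGM arm does not, so the 0–6, 0–12 and 6–12 correlations need not be equal.
- TIR is a bounded percentage, so its SD can change when its mean moves.
- Baseline TIR may rest on as little as 7 days of wear (Section 2.5, Table 1), whereas later values use the two weeks before the visit (Section 2.3).
- Everyone wears the Libre Pro at baseline, the arms wear different sensors up to month 6, and all wear the Libre 2 in months 7–12.

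If compound symmetry fails, the error term for the month-6 comparison is built from variances and correlations averaged over all three visits. The one confirmatory efficacy test, at one-sided 0.05, would then use the wrong standard error. With dropout, likelihood methods under missing at random also generally need a correct covariance for an unbiased estimate. That second effect is not quantified here.

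**Working it through.** **1. The plan's own figure.** SD of change = 16.6 × √(2 × (1 − 0.5)) = 16.6. Standard error with 72 per arm = 16.6 × √(2/72) = 2.77. For 8.6 points, 8.6/2.77 = 3.11; less 1.645 this leaves 1.46, so power is 92.8% one-sided. Also 144/(1 − 0.2) = 180. Both stated figures reproduce. They use a two-sample change-score formula, so the mixed model's covariance does not enter them.

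**2. What the random intercept estimates.** In large samples with complete data, the fitted common variance v is the mean of the three true variances, the fitted common covariance c is the mean of the three true covariances, and ρ = c/v.

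**3. The month-6 contrast.** With time as categories it is the difference between arms in Y6 − b0·Y0 − b12·Y12.

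- *Device coding as stated.* All patients are on blinded CGM at month 0 and unblinded at month 12, so the arms share both means. Then b0 = b12 = ρ/(1 + ρ), and model SE² = (2v/72) × (1 − 2ρ²/(1 + ρ)).
- *Arm-by-visit means with a shared baseline.* b0 = ρ, b12 = 0, and model SE² = (2v/72) × (1 − ρ²).

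Under either coding, true SE² = (2/72) × Var(Y6 − b0·Y0 − b12·Y12) under the true covariance. Actual one-sided error = 1 − Φ(1.645 × model SE / true SE).

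**4. One case in full (assumed SDs 16.6/20/16.6; correlations 0.5/0.4/0.6 for 0–6, 0–12, 6–12).** v = (275.56 + 400 + 275.56)/3 = 317.04. c = (166.0 + 110.2 + 199.2)/3 = 158.5. ρ = 0.500.

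- *Device coding.* b = 0.333. Model SE = 2.42. The true variance of the combination is 400 + 0.111 × 771.6 − 0.667 × 365.2 = 242.3, so true SE = √(242.3 × 2/72) = 2.59. The ratio is 0.934 and the error 6.2%.
- *Shared-baseline coding.* Model SE = 2.57. The true variance is 400 − 2 × 0.500 × 166 + 0.250 × 275.56 = 302.9, so true SE = 2.90 and the error is 7.3%.

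**5. Range.** Every SD other than 16.6 at baseline, and every correlation other than 0.5 for months 0–6, is an assumption.

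| SD at 0/6/12 | Correlation 0–6/0–12/6–12 | Device coding: model SE, true SE, error | Arm-by-visit, shared baseline: model SE, true SE, error |
|---|---|---|---|
| 16.6/16.6/16.6 | 0.5/0.5/0.5 | 2.26, 2.26, 5.0% | 2.40, 2.40, 5.0% |
| 16.6/16.6/16.6 | 0.5/0.4/0.6 | 2.26, 2.10, 3.9% | 2.40, 2.40, 5.0% |
| 16.6/16.6/16.6 | 0.5/0.3/0.8 | 2.19, 1.77, 2.1% | 2.34, 2.40, 5.4% |
| 16.6/20/20 | 0.5/0.4/0.6 | 2.57, 2.55, 4.8% | 2.73, 2.90, 6.1% |
| 16.6/20/20 | 0.3/0.2/0.6 | 2.81, 2.76, 4.7% | 2.92, 3.18, 6.5% |
| 16.6/20/16.6 | 0.5/0.4/0.6 | 2.42, 2.59, 6.2% | 2.57, 2.90, 7.3% |
| 16.6/14/14 | 0.5/0.4/0.6 | 2.05, 1.77, 2.9% | 2.17, 2.03, 3.9% |
| 16.6/19.9/16.6 | 0.5/0.5/0.5 | 2.43, 2.73, 7.2% | 2.58, 2.89, 7.1% |
| 16.6/13.3/16.6 | 0.5/0.5/0.5 | 2.13, 1.83, 2.8% | 2.26, 1.93, 2.7% |
| 16.6/19.9/16.6 | 0.4/0.4/0.7 | 2.42, 2.58, 6.2% | 2.57, 3.04, 8.3% |

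For the fifth row, 3,000 simulated trials under arm-specific coding gave 6.2% error.

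**6. Cost and gain of the unstructured model.** If compound symmetry holds, its standard error equals the random-intercept one (2.26 or 2.40). In the third row under device coding it is 1.48, against a reported 2.19.

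**The case against.** The strongest reply is that the article never says the random intercept is the only covariance term. A random intercept can sit beside heterogeneous residuals or robust standard errors, and a condensed article may leave these to an analysis plan that is not shown. That stands as a limit. But the article did choose and state a structure, and its ordinary reading is compound symmetry.

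Second, a reader might infer that the primary test has inflated type I error. The documents do not support that. The clearest inflation (6.1%, 6.5%, 7.3%) belongs to arm-by-visit coding with a shared baseline; the stated device coding gives 4.8%, 4.7% and 6.2% in the same scenarios. With separate baseline means and a plain month-6 minus month-0 contrast (b0 = 1, b12 = 0, model SE² = 4(v − c)/72), they become 4.7%, 5.6% and 5.7%. Material inflation under the device coding needs a month-6 SD that rises and then falls back by month 12.

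Third, the documents supply no evidence that compound symmetry fails: the only SD and correlation given are compatible with it. This also stands, and makes the point conditional.

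Finally, the fixed-effect coding in Section 2.8.1 may be the larger problem. That is true, but it is a separate one.

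**Conclusion.** The point holds as a conditional weakness. On its ordinary reading the primary model ties the error of the month-6 comparison to an equal-variance, equal-correlation assumption that spans a treatment switch and that nothing in the article supports. If the assumption fails, the standard error is wrong in a direction that cannot be known in advance.

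With 72 complete patients per arm and the assumed values above, actual one-sided error under the stated coding is about 2% to 6%, or about 7% if only the month-6 SD is 20% higher. It is often below 5%, with precision lost. With arm-by-visit means and a shared baseline it is about 3% to 8%. Mild departures matter little: with equal SDs the shared-baseline standard error shifts by 2–3% at most in the table.

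Two stronger conclusions do not follow. The article does not show that the test is anti-conservative, and the stated power and sample size are not in error on this account. This is a change worth making rather than one on which the trial's validity turns.

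**What to change.** In Section 2.8.1, replace the random intercept by an unstructured covariance across months 0, 6 and 12, fitted by REML with Kenward-Roger degrees of freedom. Name a random intercept with robust (sandwich) standard errors as the fallback if the model does not converge. Robust errors belong only in the fallback, because they correct the standard error but not any bias that a wrong covariance brings under dropout. Section 2.8.4, which refers to maximum likelihood, should be aligned. If an existing analysis plan already specifies such a structure, one sentence in the protocol saying so is enough.

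The cost is one line of specification and six covariance parameters instead of two, which 144 to 180 patients support easily, with essentially no loss if compound symmetry is true. The article reports enrolment still in progress and no planned interim analysis, so the change can be made before the arms are compared.

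This does not repair the fixed effects. The device indicator gives both arms one month-12 mean. Under compound symmetry with correlation 0.5, each point of true month-12 difference between arms then biases the month-6 effect by about −0.33 points (b12 = 0.5/1.5). That needs means by randomized arm and visit, and both changes should be made together.

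### The primary mixed model codes device instead of randomised arm: its interaction is aliased or off target, and its month-6 contrast is biased if the arms differ at month 12

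*Protocol article*

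**What the plan says.** Protocol article, Section 2.7, sets the target: "The null hypothesis is that the two arms will demonstrate no significant differences in the six-month change in glucose TIR". The test is made "at the one-sided significance level of 0.05".

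Section 2.8.1 gives the primary model. It has a subject-level random intercept, time of measurement at 0, 6 or 12 months, and a "time-dependent binary indicator for the type of CGM (SMBG with blinded CGM or unblinded CGM), and time-by-CGM-type interaction". Age and gender may be added. Randomised arm is not a listed term, and no coefficient or contrast is named as the primary test.

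Section 2.8.4 adds: "All primary analyses will follow the intent-to-treat principle".

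Section 2.3 and Table 1 fix who wears what. All participants wear a blinded sensor at baseline. At month 6 the CGM Group is unblinded and the Control Group blinded. At month 12 both groups are unblinded. Section 2.3 also counts the Control Group's second six months, after its switch, as part of the primary endpoint assessment.

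**The concern.** The hypothesis concerns randomised arms at month 6. The model concerns device worn, across three time points. Device separates the arms only at month 6, so the month-0 and month-12 data cannot support a full time-by-device interaction. At month 12 the model cannot tell a participant with 12 months of unblinded CGM from one with 6.

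Two things are at stake. First, someone who fits the model as written gets either aliased terms or an interaction that answers a different question, with no instruction on which estimate is primary. Second, even the right contrast read from this model depends on an assumption that the randomised comparison does not need: that both arms have the same mean TIR at month 12.

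**Working it through.** **Inputs (Section 2.7 unless stated).** 72 per arm and a difference of 8.6 points: "A sample size of 144 patients (72 per arm) will have over 90% power to detect a difference of 8.6% in 6-month TIR changes". SD 16.6: "We estimate a standard deviation of 16.6% for baseline TIR based on our pilot data". Correlation 0.5: "assume a moderate correlation of 0.5 between baseline and 6-month TIR values". Dropout: "To allow a 20% dropout rate, a total of 180 patients will be randomized". One-sided alpha 0.05. Device pattern at months 0, 6, 12 (Section 2.3, Table 1): CGM Group 0, 1, 1; Control Group 0, 0, 1.

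**1. The plan's own figure.** SD of change = 16.6 × √(2 × (1 − 0.5)) = 16.6. SE of the difference = 16.6 × √(2/72) = 2.77. Power = Φ(8.6/2.767 − 1.645) = Φ(1.463) = 92.8%. 144/(1 − 0.2) = 180. Both stated figures reproduce.

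**2. Categorical time.** The columns are intercept, month 6, month 12, device, device × month 6 and device × month 12: six in all. The occupied cells are (0, blinded), (6, blinded), (6, unblinded) and (12, unblinded): four.
- The month-12 column equals device × month 12.
- The device column equals device × month 6 plus device × month 12.
- The rank is therefore 4 of 6. The device main effect and both interaction coefficients are not estimable individually. Device plus device × month 6 is estimable.

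**3. Linear time.** Write S0, S6 for the blinded/SMBG cell means and C6, C12 for the unblinded cell means. Four parameters fit four cells, so:
- interaction = [(C12 − C6) − (S6 − S0)]/6
- device main effect = 2·C6 − C12 − S0
- main effect + 6 × interaction = C6 − S6

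Only the last is the month-6 comparison. Three examples, with an illustrative baseline of 30:

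| Cell means S0, S6, C6, C12 | True effect | Main effect | Interaction per month | Main + 6 × interaction |
|---|---|---|---|---|
| 30, 30, 38.6, 38.6 (constant effect) | 8.6 | 8.6 | 0 | 8.6 |
| 30, 35, 43.6, 43.6 (education adds an assumed 5, then plateaus) | 8.6 | 13.6 | −0.83 | 8.6 |
| 30, 35, 35, 35 (same, no CGM effect) | 0 | 5.0 | −0.83 | 0 |

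**4. Bias in the recovered contrast.** Let d0, d6, d12 be the CGM-minus-control differences in mean TIR. Device coding sets d0 = d12 = 0. Randomisation justifies the first in expectation; nothing justifies the second. A random intercept gives equal correlation r between visits, so generalised least squares estimates d6 − [r/(1 + r)] × (d0 + d12). With r = 0.5 the weight is 0.5/1.5 = 1/3. The SE is 16.6 × √[(2/72) × (1 − 2 × 0.5²/1.5)] = 2.26.
- d6 = 8.6, d12 = +3: 8.6 − 1.0 = 7.6.
- d6 = 8.6, d12 = −3: 8.6 + 1.0 = 9.6.
- d6 = 0, d12 = −3: bias +1.0; one-sided type I error 1 − Φ(1.645 − 1.0/2.259) = 11.5%.
- d6 = 0, d12 = −6: bias +2.0; one-sided type I error 1 − Φ(1.645 − 2.0/2.259) = 22.4%.

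The 3- and 6-point values are assumptions; the article gives no expected month-12 difference.

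**5. Randomised arm by categorical visit.** The rank is 6 of 6. The arm × month-6 term equals the arm difference in six-month change, with SE 2.77 and power 92.8%, as in step 1. With a common baseline mean the rank is 5 of 5 and the SE is 2.40. Neither estimate moves with the month-12 means.

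**The case against.** The strongest reply is that the model still contains the answer. All four cells are fitted, and by schedule device and arm coincide at month 6. The unblinded-minus-blinded contrast at month 6 is therefore available under either time coding, and the hypothesis in Section 2.7 says what is wanted. This stands. A reader might infer that the model cannot estimate the six-month effect at all, or that the trial would run at 5% power (the linear-time interaction at a constant 8.6-point effect) or report a false 5.0-point effect (the linear-time main effect under an education plateau). Those results need one coefficient, read alone, to be the test. The article does not say that, and the correct contrast in the same scenarios returns 8.6, 8.6 and 0. Naming the contrast may also be left to an analysis plan that is not shown.

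It is also fair that a 3-point month-12 difference does little harm to power: at 7.6 points, Φ(7.6/2.259 − 1.645) is about 96%. The inflated type I error needs no six-month effect together with a control arm that is better at month 12 despite less CGM exposure.

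A reader might infer a breach of intention to treat. The text does not establish one: a time-dependent indicator can follow the assigned device sequence, and the conflict arises only if actual use is coded. Nor does the article show that durability at 12 months cannot be assessed. That is a secondary objective (Section 2.2), and Section 2.8.1 covers only the primary endpoint.

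Finally, coding month 0 by assigned device would make the month-6 interaction the right contrast (rank 5 of 6, month-12 interaction still aliased). But that does not fit an indicator that changes with time when everyone starts blinded.

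The shared month-12 mean is untouched by these replies. It follows from the stated terms and remains even when the correct contrast is read.

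**Conclusion.** The concern holds in a limited form. The stated fixed effects omit randomised arm. They are rank-deficient under categorical time (4 of 6), and under linear time their interaction is not the hypothesised contrast. The month-6 contrast can be recovered, but it carries a bias of minus one third of the month-12 arm difference: 1 point for each 3 points, in either direction. Type I error reaches 11.5% to 22.4% only under a null six-month effect with control an assumed 3 to 6 points higher at month 12.

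The one-third weight rests on a random-intercept covariance with r = 0.5, 72 per arm and complete data at all three visits; in general the weight is r/(1 + r). Equal month-12 means should not be presumed, because one arm has then had twice the exposure and the durability of benefit is itself a study goal. The defect lies in the analysis model, not in the sample size. It should be fixed before database lock.

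**What to change.** In Section 2.8.1, replace the device indicator and its interaction with randomised arm, categorical visit and arm × visit. Name the arm difference in change from baseline at month 6 as the single primary contrast. State that arm is coded as randomised, which settles the intention-to-treat point.

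Put month-12 and post-crossover control data in a secondary model that contains randomised arm, and align the sentence in Section 2.3 that counts the Control Group's months 6–12 as primary assessment. A common baseline mean would lower the SE from 2.77 to 2.40, and an unstructured covariance would relax the equal-correlation assumption. Both are optional.

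The cost is a change of wording. No further participants or data are needed, and power is 92.8% at 8.6 points. With last follow-up planned for April 2027 (Section 3), the change can still be made before lock.
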